**Fig. 1 Fig1:**
[figure not shown]
Study flow chart. *CFR* coronary flow reserve, *IMR* Index of Microvascular Resistance, *FFR* Fractional Flow Reserve, *AMI* acute myocardial infarction, *PCI* percutaneous coronary intervention, *CK*-*MB* creatine kinase myoband, *cTn I* cardiac troponin I

Patient identification and enrollment: All consecutive patients with stable ischemic heart disease and T2DM or pre-T2DM referred for coronary angiography will be screened as potentially eligible for the study. Assessment of coronary stenosis severity using Fractional Flow Reserve (FFR) and the status of the microcirculation including measurement of coronary flow reserve (CFR) and Index of Microvascular Resistance (IMR) [10, 11] will be performed with the same pressure guidewire as part of the diagnostic process. Revascularization will be considered whenever a FFR ≤0.80 is found in a stenosis amenable to PCI. Eligible patients requiring PCI will be informed of the characteristics of the study and invited to participate.Randomization: Patients will be randomly assigned (1:1 ratio) to receive either Clopidogrel (600 mg loading dose followed by a daily dose of 75 mg) or Ticagrelor (180 mg loading dose followed by a dose of 90 mg b.i.d). The groups will be balanced according to the presence or absence of obesity [12] (Body Mass Index ≥ 30 kg/m^2^) [12] with the implementation of a dedicated randomization list. Patients who are already on oral treatment with Clopidogrel 75 mg/day are allowed to enter the protocol. According to randomization arm these patients will be assigned, after baseline assessment of microcirculation, to continue Clopidogrel 75 mg/day or be switched to Ticagrelor (180 mg loading dose followed by a dose of 90 mg b.i.d).PCI procedure: PCI procedure will be deferred for at least 48 h after the first administration of the study drug treatment in order to allow approximately 5 mean-half life times of their active metabolites, similar to a previously published study [9].3.1.Pre-PCI: Multimodal physiological evaluation (FFR, CFR, IMR) will be repeated.3.2.PCI: For all patients undergoing PCI, unfractioned heparin will be administered at the time of PCI. The PCI procedures will be performed using standard techniques using and second generation Drug Eluting Stents. Balloon pre-dilatation will be mandatory before stent implantation using a semi-compliant balloon with a diameter smaller than 75% of the distal reference vessel size in order to avoid confounding effects related to pre-dilation [13]. Post-dilation will be performed according to clinical practice although it will not be mandatory. All PCI characteristics (materials and techniques) will be recorded.3.3.Post-PCI: After stent implantation, multimodal intracoronary physiological evaluation will be repeated (FFR, CFR, IMR).

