## Sample size and statistical analysis

As no studies are currently available reporting on the impact of Ticagrelor on microvascular function compared to Clopidogrel, we based our sample size calculation on a previous study [10] showing that the intracoronary administration of Nicorandil after PCI resulted in a difference of 10 units in deltaIMR with respect to the control group. Assuming a difference of 10 in deltaIMR, in the experimental vs. control group, and a standard deviation of 10 a total of at least 20 patients per group would be needed to achieve an 80% power at a 2-sided alpha of 0.025, which accounts for the multiple primary endpoint design with a Bonferroni correction. Therefore, we aim to enroll 25 patients per group in order to take into account a 25% of potential missing data or major protocol violation due to clinical reasons (for example: clinical instability of patient between index and PCI procedure leading to urgent revascularization before completion of the protocol).

Any subject who took no trial medication will be eliminated from the full analysis set. Although a low or null proportion of exclusions due to treatment non-compliance is expected, any potential biases arising from this exclusion will be addressed. Imputation techniques will be used in an attempt to compensate for missing data. Regarding missing data, for primary endpoints, listwise deletion will be used meanwhile for the rest of analyses, listwise deletion or multiple imputation will be considered, depending on the type of missing process and on the quantification of the efficiency loss due to case deletion in each case. An investigation will be made concerning the sensitivity of the results of analysis to the method of imputation, especially if the number of missing values is substantial.

Being PREDICT a multicenter trial, the influence of the centre on the treatment effect and other endpoints will be addressed, and further adjustment will be done in the subsequent analysis, if necessary. Special attention will also be paid to the role of baseline measurements of the primary variable and diabetes treatment. Moreover, obese patients and those with previous myocardial infarction are subgroups of interest and their influence on the primary variables will be addressed and interpreted. However, subgroup analyses here have a exploratory nature, and therefore, interpreted cautiously.

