A diagram of the participant flow showing for each group, the number of participants who were randomly assigned, received intended treatment, and were analyzed for the primary outcome will be provided, as recommended by the CONSORT 2010 statement.

Categorical variables will be reported as frequencies and percentages. Continuous variables will be expressed as mean ± SD or as median (Q_1_–Q_3_), according to the normality of their distribution, which will be tested with the Shapiro–Wilk test. Bartlett’s test will be performed to demonstrate homogeneity of variances between more than two groups. Primary endpoints will be assessed using the Student *t* test, if the samples are normally distributed or their variances are homogeneous; or Mann–Whitney U test, otherwise. P values will be corrected in order to account for the multiple endpoint. For the analysis of secondary variables, comparisons between continuous variables will be performed using the (paired or unpaired) Student *t* test or Mann–Whitney U test. The IMR at baseline, before PCI, and after PCI will be compared with an ANOVA for repeated measures or with the Friedman test, as appropriate. Comparisons between categorical variables will be evaluated using the Fisher exact test or the Pearson Chi square test, as appropriate. Correlations between continuous variables will be assessed using the Pearson or the Spearman rank correlation test. A 2-way ANOVA for repeated measures will be used to detect changes in IMR levels over time in the two study groups. Finally linear and logistic regression models will be carried out in order to identify predictors of periprocedural myonecrosis and delta-IMR. Analysis will be performed both in the full analysis set and a per protocol analysis and any differences between them would be the subject of explicit discussion and interpretation. In case of having multiple stenoses in some patient, additional adjusted analysis will be provided. Statistical analyses will be performed using the R statistical software [17] and p values <0.05 (2-tailed) will be considered significant. Whenever possible, estimates will be accompanied by confidence intervals.

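### The primary test is chosen from the data by a rule that admits Student's t under unequal variances and otherwise moves to a rank test that does not test the planned mean difference

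*Protocol article*

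**What the plan says.** All of this is in the protocol article, section 'Sample size and statistical analysis', unless stated otherwise.

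- **Test rule.** Primary endpoints are compared by Student's t test "if the samples are normally distributed or their variances are homogeneous"; in any other case by Mann–Whitney U. No unequal-variance version of the t test is named.
- **Sizing.** The sample size is built on a mean difference: "Assuming a difference of 10 in deltaIMR, in the experimental vs. control group, and a standard deviation of 10". The result is 20 patients per group for 80% power.
- **Significance level.** Each of the two primary endpoints has its own share of the overall 5%, described as a "2-sided alpha of 0.025, which accounts for the multiple primary endpoint design with a Bonferroni correction".
- **Arms.** Allocation is 1:1 (flow-chart text under 'Population recruitment and flow chart'). Enrolment is 25 per group to allow for 25% missing data or major violations. The primary endpoints use listwise deletion, so the analysed arms need not be equal.
- **Estimates.** Confidence intervals are promised wherever possible.

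**The concern.** Student's t test with a pooled variance relies on roughly normal data (or enough patients) and on equal variances. The rule asks for only one of the two, which has two consequences.

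1. Normal data with visibly different spread in the arms are still analysed with a pooled variance. If the analysed arms also differ in size, the standard error is wrong.
2. Mann–Whitney is reached only when normality and equal variance both fail. It asks whether values in one arm tend to exceed those in the other. When shapes and spreads differ, that is not a test of equal means, and it does not estimate the 10-unit difference used for sizing.

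The rule runs separately on the two primary endpoints, so the mechanistic and protective effects could be tested by different methods and answer different questions. What is at stake is mainly that the primary analysis and its estimand are not fixed before the data are seen. Under some conditions the type I error is affected too.

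**Working it through.** **1. The plan's own figure.** Inputs: difference 10, SD 10, two-sided alpha 0.025, power 80%.

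n per group = 2 × (z₀.₉₈₇₅ + z₀.₈₀)² × SD² / difference² = 2 × (2.241 + 0.842)² × 100/100 = 19.01, so 20. The stated figure reproduces. Power at 20 per group is 82.1% by the normal approximation and 79.3% by the exact noncentral t. It is a calculation for a difference in means.

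**2. Where the rule sends the data.**

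| | Variances equal | Variances unequal |
|---|---|---|
| Normal | Student's t | Student's t |
| Not normal | Student's t | Mann–Whitney |

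With normal data the variance result makes no difference to the choice of test.

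**3. Why arm sizes matter in the 'normal, unequal' cell.** Assume SD 20 v 10 (not in the document). With 25% loss from 25 per arm about 19 remain, 38 in total; take 16 v 22 as an uneven split.

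- Smaller arm more variable: pooled variance = (15 × 400 + 21 × 100)/36 = 225. Pooled SE = √[225 × (1/16 + 1/22)] = 4.93. True SE = √(400/16 + 100/22) = 5.44. The SE is too small, so the test rejects too often.
- Larger arm more variable: pooled variance = (15 × 100 + 21 × 400)/36 = 275. Pooled SE = 5.45, true SE = 4.94. The test rejects too seldom.
- Equal arms, 20 v 20: pooled variance = 250, and pooled SE = true SE = 5.00. Hence there is little distortion under 1:1.

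**4. Simulated type I error.** Equal means, nominal 2.5%; most settings used 10,000 runs (simulation SE about 0.16 points) or 5,000. Assumed: Shapiro–Wilk in each arm and Bartlett between arms, both at 0.05; pooled-variance t; the SD ratios, arm sizes and shapes shown.

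| Data, SD ratio, evaluable | Rule as written | 'and' rule | Welch |
|---|---|---|---|
| Normal, 1 to 3, 20/20 or 25/25 | 2.5–3.1% | 2.6–3.6% | 2.4–2.9% |
| Normal, 2, 16 v 22, smaller arm more variable | 4.8% | not run | 2.6–3.0% |
| Normal, 2, 16 v 22, larger arm more variable | 1.8% | not run | not run |
| Normal, 2, 25 v 19, smaller arm more variable | 4.3% | 3.7% | 2.5% |
| Normal, 2, 25 v 19, larger arm more variable | 1.7% | 2.0% | 2.5% |
| Normal, 2, 25 v 15, smaller arm more variable | 6.1% | 4.9% | 2.7% |
| Lognormal, 1, 20/20 | 1.8–2.2% | 2.2–2.6% | 1.9–2.2% |
| Lognormal, 2, 20/20 | 7.1–8.1% | 9.7–11.4% | 3.5–3.7% |
| Lognormal, 2, 25 v 19, smaller arm more variable | 10.1% | 13.6% | 4.2% |
| Lognormal, 3, 20/20 | 16.1% | 17.4% | 4.8% |

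A milder lognormal (log-SD 0.6) at 19 v 19 and SD ratio 2 gave 6.6%, hence the range of about 6–10% for skewed data at that ratio.

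**5. Source of the skewed-data excess.** In the lognormal, SD ratio 2, 20/20 setting, Student's t used unconditionally gave 3.6–3.8% and Mann–Whitney used unconditionally gave 9.7–11.4%. The rule chose Student's t in 35–36% of trials. The excess therefore comes mainly from the Mann–Whitney branch. The 'and' rule sends more trials there and does worse.

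**The case against.** The other side has good points, and several stand.

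- **Under the plan's own assumptions nothing is inflated.** With 1:1 allocation and a single SD of 10, the error rate is about 2–3%. This stands. A reader might infer that the error rate is simply not 2.5%; the document gives no arm-specific SD, shape or attrition that would support that.
- **A drug with no effect at all gives both arms the same distribution.** The equal-SD results then apply, and there is no excess. A drug that trims the largest IMR rises would also lower the mean, which is a real effect. This stands. The inflated figures concern equal means with unequal spread, a narrower null.
- **The adverse imbalance is uncommon.** With random 25% loss from 25 per arm, a gap of six or more with the more variable arm the smaller occurs in about 3.6% of trials. Averaged over such loss at SD ratio 2 with normal data, the error rate is 2.9%. In the reverse direction the test is conservative. This also stands.
- **Weak pre-tests are not the cause.** One might blame low power of the preliminary tests. At 20 per arm Bartlett has 84% power at SD ratio 2, and with normal data the 'or' overrides its result anyway.
- **The article does not say which variance check serves the two-arm comparison.** It states that Bartlett's test "will be performed to demonstrate homogeneity of variances between more than two groups". A condensed article may leave that detail to the full protocol, so it is not counted as a fault here.

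The article also plans repeated-measures ANOVA, linear models for delta-IMR and attention to baseline values. These are useful, but none is designated as the primary analysis, so none repairs the rule.

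**Conclusion.** The concern holds in a limited form. It does not depend on any assumption that the stated rule lets the data choose the primary test, accepts Student's t with clearly unequal variances, and in one branch abandons the mean difference used for sizing. This is a rule fixed badly, not a detail left to another document.

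The error-rate consequence is conditional. It is near nominal (about 2–3%) with equal SDs, or with normal data and equal arms. It is 1.8% to 4.8% with normal data, SD ratio 2 and 16 v 22 evaluable, and about 6–10% with skewed data and SD ratio 2. More extreme assumptions give more (16.1% for lognormal data at SD ratio 3). The SD ratios, skewness, evaluable numbers and pre-test levels are all assumptions.

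It should be fixed before unblinded analysis, but it does not undermine the design. A reader might also infer that the one word 'or' is the whole fault. It is not: 'and' helps somewhat when the smaller arm is more variable in normal data, but it is no better with equal arms and worse with skewed data.

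**What to change.** Delete the test-selection rule for the primary endpoints and name one analysis of the mean difference in deltaIMR for both:

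- Welch's unequal-variance t test, or a baseline-adjusted linear model with heteroscedasticity-robust standard errors. State one, not a choice between them.
- Report the difference with a 97.5% confidence interval, matching the Bonferroni level of 0.025 per endpoint.
- Keep Mann–Whitney as a named sensitivity analysis, whatever the distributional checks show.
- Use normality and variance checks for description only.

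Welch is not exact with strong skew (3.5–3.7% at SD ratio 2 and 4.8% at SD ratio 3, lognormal, 20/20), but it was much closer to 2.5% than the rule in those settings.

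The cost is wording. No further patients are needed: at 20 per arm with equal SDs, simulated power was 80.0% for Welch against 80.1% for the pooled t test. The 0.1-point difference is the relevant figure; both levels differ slightly from the exact 79.3% through simulation error.

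### For paired secondary comparisons the only two-sample rank test named is Mann-Whitney U, which assumes independent groups; the gap is minor and one sentence closes it

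*Protocol article*

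**What the plan says.** All the test choices stand in the protocol article under Sample size and statistical analysis.

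- Primary endpoints: "Primary endpoints will be assessed using the Student" t test or the Mann-Whitney U test. Both endpoints in Table 1 contrast a change in resistance between the two arms.
- Secondary continuous variables: "comparisons between continuous variables will be performed using the (paired or unpaired) Student" t test, with Mann-Whitney U as the alternative. No other two-sample rank test is named in the document.
- IMR at its three time points: "compared with an ANOVA for repeated measures or with the Friedman test, as appropriate". A two-way repeated-measures ANOVA of IMR by arm is also planned.
- Significance: "p values <0.05 (2-tailed) will be considered significant".

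The repeated readings come from the flow chart steps under Population recruitment and flow chart. FFR, CFR and IMR are measured at the diagnostic procedure and again before PCI. Step 3.3 adds a third reading: "After stent implantation, multimodal intracoronary physiological evaluation will be repeated (FFR, CFR, IMR").

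**The concern.** The words in parentheses show that some secondary comparisons will be made within patients. For those the parametric test is named correctly, but its rank counterpart is not. Mann-Whitney U assumes two independent samples. Given a patient's readings before and after an event, it treats them as coming from two different people and leaves the between-patient spread in the error term.

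If the two readings are positively correlated, as repeated readings in one patient normally are, the p value is too large. A real change within patients could then be reported as non-significant. The contrasts exposed are those with two time points that no other sentence covers: changes in FFR, changes in CFR, and pairwise changes in IMR if the three-time-point test is followed up.

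**Working it through.** **1. The number of pairs.** The plan asks for 20 evaluable patients per group (difference 10, SD 10, two-sided alpha 0.025, 80% power) and enrols 25 per group. The normal formula reproduces its figure:

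n = 2 (z₀.₉₈₇₅ + z₀.₈₀)² (SD/difference)² = 2 × (2.241 + 0.842)² × (10/10)² = 19.01, rounded up to 20 per group.

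The t-based solution is 20.3, with 79.3% power at 20. The point does not turn on this figure. It only shows that a within-arm contrast has about 20 to 25 pairs, and one pooled over arms at most 50.

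**2. Direction of the error.** Take two readings with equal variance σ² and within-patient correlation ρ. The mean change over n pairs has variance 2σ²(1 − ρ)/n. An independent-samples analysis works with 2σ²/n, so its standard error is too large by the factor 1/√(1 − ρ):

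- ρ = 0.3: 1/√0.7 = 1.20
- ρ = 0.5: 1/√0.5 = 1.41
- ρ = 0.7: 1/√0.3 = 1.83

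At ρ = 0 the factor is 1 and nothing is lost.

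**3. Size of the error for the rank tests.** This was simulated with 4,000 replicates per setting, so the Monte Carlo standard error is at most √(0.25/4000) = 0.8 percentage points. Pairs were log-normal (log-SD 0.6) and both tests were two-sided at 0.05. Correlation, log-SD and shift are assumptions. The 0.05 level is the plan's.

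25 pairs, shift 0.5 SD:

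| ρ | True type I error, Mann-Whitney | True type I error, signed-rank | Power, Mann-Whitney | Power, signed-rank | Share of power lost |
|---|---|---|---|---|---|
| 0 | 4.4% | 4.2% | 39% | 36% | none |
| 0.3 | 2.0% | 4.8% | 38% | 49% | 22% |
| 0.5 | 0.7% | 5.0% | 35% | 60% | 42% |
| 0.7 | 0.1% | 5.0% | 33% | 81% | 59% |
| 0.9 | about 0 | 4.7% | 31% | 99.8% | 69% |

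The last column is 1 − (Mann-Whitney power / signed-rank power), from unrounded powers. For example, at ρ = 0.5 it is 1 − 0.351/0.604 = 0.42.

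50 pairs, same shift: 73% against 90% at ρ = 0.5, 79% against 99% at 0.7, and 90% against 100% at 0.9. The share lost is then 10% to 20%.

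**4. Which analyses are exposed.**

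- Both primary endpoints compare a change between arms. The groups are independent and Mann-Whitney is valid.
- The secondary endpoints in Table 1 are biomarker-assessed necrosis, absolute resistance after PCI and incidence of IMR above 29. They read as between-arm comparisons. Mann-Whitney is valid for the continuous ones, and the plan gives categorical variables the Fisher or chi-square test.
- IMR over three time points has the Friedman test, which is a related-samples rank test.
- Two-time-point contrasts within patients in FFR, CFR or IMR have no suitable rank test. This is the gap.

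**The case against.** The strongest defence is that nothing of consequence is touched. No endpoint in Table 1 is a two-time-point contrast within patients, and FFR and CFR are measured but are not listed endpoints. The article names no specific paired test that it will run, and the need for one is inferred from a parenthesis. The secondary sentence gives no explicit rule that sends non-normal pairs to Mann-Whitney, so it may simply be shorthand in a condensed article. A competent analyst would probably use the right test anyway, and an error in the conservative direction creates no false positives.

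Most of this stands, and it is why the point is minor. It does not remove the point. The sentence provides for paired comparisons and names a rank test that does not fit them. That is something stated badly, not a detail left for a fuller plan.

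Three stronger readings are tempting, and the documents do not support them:

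- *The plan has no valid rank test for data within patients.* It has one: Friedman, for IMR over the three time points.
- *Comparisons within patients lose most of their power.* Step 3 shows no loss at zero correlation. More than half is lost only with strong correlation and few pairs or a small shift, for example ρ of 0.7 or more with 20 to 25 pairs. The documents give no correlation.
- *Biomarker changes before and after PCI would be tested wrongly.* The in-hospital step describes samples taken at 8 and 24 h after the intervention. It states no earlier sample and plans no 8 against 24 h test.

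**Conclusion.** The point holds in a narrow form. For paired secondary continuous variables the article names only an independent-samples rank test. If that is followed on non-normal, positively correlated pairs, the p values are conservative. In the 25-pair setting, the true error rate at a nominal 5% is between about 0 and 2% for correlations from 0.3 to 0.9. The power loss runs from nothing to over two thirds, depending on correlation, number of pairs and shift. These figures rest on assumed log-normal data, and the documents give none of those inputs except the approximate number of patients.

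The sample size, the primary analysis and the between-arm secondary endpoints stand as planned. The impact is minor: it is confined to supporting two-time-point comparisons within patients.

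**What to change.** Replace the secondary-variable sentence with wording that separates the two designs, for example: *Between arms: unpaired t test or Mann-Whitney U test. Within patients, two time points: paired t test or Wilcoxon signed-rank test.* Keep the Friedman test for IMR over three time points.

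Under the same assumptions, the signed-rank test holds its error rate at about 4% to 6% at every correlation examined. The cost is one sentence, with no change to sample size, data collection or patient burden.
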